## Abstract

**Background:**

Pelvic Organ Prolapse (POP) is estimated to affect 41%–50% of women aged over 40. Findings from the multi-centre randomised controlled “Pelvic Organ Prolapse PhysiotherapY” (POPPY) trial showed that individualised pelvic floor muscle training (PFMT) was effective in reducing symptoms of prolapse, improved quality of life and showed clear potential to be cost-effective. However, provision of PFMT for prolapse continues to vary across the UK, with limited numbers of women’s health physiotherapists specialising in its delivery. Implementation of this robust evidence from the POPPY trial will require attention to different models of delivery (e.g. staff skill mix) to fit with differing care environments.

**Methods:**

A Realist Evaluation (RE) of implementation and outcomes of PFMT delivery in contrasting NHS settings will be conducted using multiple case study sites. Involving substantial local stakeholder engagement will permit a detailed exploration of how local sites make decisions on how to deliver PFMT and how these lead to service change. The RE will track how implementation is working; identify what influences outcomes; and, guided by the RE-AIM framework, will collect robust outcomes data. This will require mixed methods data collection and analysis.

Qualitative data will be collected at four time-points across each site to understand local contexts and decisions regarding options for intervention delivery and to monitor implementation, uptake, adherence and outcomes. Patient outcome data will be collected at baseline, six months and one year follow-up for 120 women. Primary outcome will be the Pelvic Organ Prolapse Symptom Score (POP-SS). An economic evaluation will assess the costs and benefits associated with different delivery models taking account of further health care resource use by the women. Cost data will be combined with the primary outcome in a cost effectiveness analysis, and the EQ-5D-5L data in a cost utility analysis for each of the different models of delivery.

**Discussion:**

Study of the implementation of varying models of service delivery of PFMT across contrasting sites combined with outcomes data and a cost effectiveness analysis will provide insight into the implementation and value of different models of PFMT service delivery and the cost benefits to the NHS in the longer term.

## Background

Pelvic organ prolapse (POP) is a common condition affecting 41%–50% of women over the age of 40 [1, 2]. POP is defined as the symptomatic descent of one or more of the anterior or posterior vaginal walls, apex of the vagina or the uterus (cervix) [3]. A rising number of POP cases result in surgery (15 to 49 cases per 10,000 women-years) [4–6]. As well as having associated morbidity, surgery is often prone to failure; around 30% of women undergo repeat operations, and the time intervals between repeat procedures shorten with each successive repair [5]. In addition, repair of one type of prolapse may predispose the woman to the development of a different type of prolapse in another compartment of the vagina [5]. There remain concerns surrounding the use of synthetic mesh, one option for prolapse surgery. Mesh-related complications are frequently reported, with up to a 35% removal rate [7] resulting in the Chief Medical Officer in Scotland (UK) requesting that all Health Boards consider suspending routine use of polypropylene mesh implants for the management of pelvic organ prolapse and incontinence in June 2014 [8].

Given these concerns, there is an ever more pressing need for evidence-based non-surgical options to be made available to women [9]. A recent definitive trial has shown that pelvic floor muscle training is an effective and potentially cost effective treatment and should be recommended as a first line treatment for POP [10]. The Pelvic Organ Prolapse PhysiotherapY (POPPY) trial was a multi-centre randomised controlled trial of the effectiveness and cost-effectiveness of individualised pelvic floor muscle training (PFMT) delivered by specialist physiotherapists compared to a lifestyle advice leaflet in newly diagnosed women with symptomatic stage I, II or III prolapse [10]. POPPY constitutes the largest, most rigorous, pragmatic trial of PFMT for prolapse, and as such provides the necessary evidence to inform future practice. Individualised PFMT was found to be effective in reducing women’s symptoms of prolapse, and providing perceived improvements in prolapse and related quality of life. The PFMT intervention also shows potential to be a cost-effective treatment.

However, knowledge of efficacy and effectiveness is not enough to ensure implementation of this evidence into practice. PFMT provision varies across the UK as there is limited availability of specialist physiotherapy services to meet the known levels of demand [11, 12]. Delivery methods that can enhance service capacity and increase availability and choice for women are required. Such delivery methods also need to be tested to ensure that the outcomes achieved under trial conditions are maintained.

This study aims to maximise the delivery of effective PFMT for women with POP through the study of its implementation in a number of diverse settings using an evidence-based PFMT protocol. This will involve developing different service delivery models, incorporating a variety of staff skill mixes and sessions to increase capacity, with the format of delivery being determined locally. These will be addressed through the following specific study aims:To explore the potential for different groups of staff skill mix to deliver PFMT without compromising the achievement of clinical outcomesTo explore fidelity or variation to PFMT protocol (e.g. number and type of sessions) and the impact of any variationsTo establish the levels of support required by non-specialist physiotherapists to deliver PFMTTo explore the acceptability and outcomes for women of different delivery modelsTo establish the costs and benefits associated with each model of deliveryTo contribute to knowledge of how and why implementation processes are successful (or not) through exploring what works, for whom and in what circumstances.

Implementation Science is an emerging field aiming to foster understanding of the complex and multi-level processes involved in the uptake and spread/scale-up of evidence-based interventions and programmes [13]. It aims not only to reduce a gap in quality of care, but also to advance the science of implementation by providing generalisable knowledge that will be useful for other settings and contexts. It can help to identify barriers to implementation but should also extend this to understand how and why implementation processes are effective [14]. To do this we need to study implementation strategies and the contexts and processes in which implementation strategies are delivered. Such research can advance the adoption, sustainability and wider roll out of cost-effective evidence based interventions and are a necessary step in the MRC’s evaluation of complex interventions framework [15].

## Methods/design

### Study design

The study will involve: A) A Realist Evaluation (RE) using case studies of implementation of PFMT delivery in three varying NHS settings; B) An outcomes study of PFMT delivery in the different models; C) An economic evaluation to compare the costs and benefits of the different models.

### A) Realist Evaluation using case studies of implementation

The RE will involve substantial local stakeholder engagement, allowing local sites to make decisions on how to deliver PFMT (within their resources) and will elicit local folk theories around: how implementation is supposed to work; track how the implementation is working (including fidelity to the PFMT protocol); and understand what influences outcomes.

### Setting

The Realist Evaluation will be based at three NHS sites in the UK with either specialist pelvic floor or women’s health services, and selecting sites reflecting a mix of urban/rural locations, previous involvement/non-involvement in POPPY and current differences in service delivery models (see Table 1). A lead specialist physiotherapist based at each location will facilitate liaising with local service managers/consultants and staff to take part in developing a local model of PFMT service provision; the research team will consent those participating into the study.

**Table 1 Tab1:** Realist Evaluation Study site descriptions

Site	Urban/rural	POPPY experience	Current dominant model
1	Urban	POPPY recruiting centre	Primary and secondary care provision of specialist physiotherapy referred by primary care and acute services with a mix of 1:1 and group provision available. Women not routinely sent to physiotherapy as first line treatment. Several POPPY physiotherapists providing current input to women with POP
2	Urban	Large involvement in medically driven trials but no focus on physiotherapy based trials	Currently has some specialist physiotherapy involvement but greater specialist nurse-led service for women
		No POPPY involvement	
3	Rural	No POPPY involvement and limited other trial involvement	Current interest in re-design and expanding to junior grade physiotherapists and other nursing staff (as practitioners with special interest)

*POP* Pelvic Organ Prolapse, *POPPY* Pelvic Organ Prolapse PhysiotherapY trial

### B) Outcomes study

Outcomes data will be collected before and after women receive the PFMT intervention in each location/model of service delivery to establish whether the improvements observed in the POPPY trial are also observed under different models of delivery and in non-trial real world NHS settings (see Table 2).

**Table 2 Tab2:** Outcomes Study site descriptions

Site	Urban/rural	POPPY experience	Current dominant model
1	Urban	POPPY recruiting centre	Primary and secondary care provision of specialist physiotherapy referred by primary care and acute services with a mix of 1:1 and group provision available. Women not routinely sent to physiotherapy as first line treatment. Several POPPY physiotherapists providing current input to women with POP
2	Urban	Large involvement in medically driven trials but no focus on physiotherapy based trials	Currently has some specialist physiotherapy involvement but greater specialist nurse-led service for women
		No POPPY involvement	
3	Rural	No POPPY involvement and limited other trial involvement	Current interest in re-design and expanding to junior grade physiotherapists and other nursing staff (as practitioners with special interest)
4	Urban	No POPPY involvement	Currently has some specialist physiotherapy involvement, looking to increase capacity for PFMT provision with other staff groups
5	Urban	No POPPY involvement	Currently has some specialist physiotherapy involvement, looking to increase capacity for PFMT provision with other staff groups

*PFMT* Pelvic Floor Muscle Training, *POP* Pelvic Organ Prolapse, *POPPY* Pelvic Organ Prolapse PhysiotherapY trial

### Recruitment/sampling

Women who are awaiting treatment for prolapse at study sites will be potential recruits if they are eligible and provide written, informed consent to take part. We aim to recruit 120 women to the outcomes study.

### Inclusion criteria

Women 18 years of age or above, presenting with symptomatic stage I, II or III prolapse of any type who are suitable to be referred for PFMT and who are willing to take part in the research and comply with necessary data collection.

### Exclusion criteria

Women who are pregnant or less than one year postnatalWomen who have prolapse greater than stage III, who have pelvic cancer, cognitive impairment or neurological disease (as indicated by referral source or patient/carer reported at assessment consultation)

### Sample size

We have assumed that the minimum clinically important difference in the POP − SS is 2 [16] and that the standard deviation of the differences in POP − SS between baseline and one year will be 5.5 (as observed in POPPY). A sample size of 120 paired observations (with 2-sided alpha = 0.05) will therefore provide 80% power to detect important differences in POP − SS between baseline and one year.

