### B) Outcomes data

Descriptive statistics will be tabulated for all outcomes at each time point, showing means and SDs for POP − SS and EQ − 5D-5 L, proportions for POP − Q, the need for further treatment, and frequencies for the number of NHS contacts. Differences (and correlations where appropriate) between baseline and 6 − months and between baseline and 12 − months will be calculated. We will initially examine the differences before and after intervention using paired t-tests and chi-square tests. We will fit appropriate generalised linear models on the difference between outcomes before and after intervention, adjusting for baseline measurements and potential confounders (e.g. demographic factors, study site). If possible, we will also explore the effect of different levels of adherence to PFMT using structural mean models [28]. Complete case analyses will be performed throughout, with missing data being addressed in secondary analyses using multiple imputation methods.

POP − SS and EQ − 5D 5L will be treated as continuous data, POP − Q as ordinal, NHS contacts as count data and the need for further treatment (e.g. surgery or pessary) as binary data. In order to facilitate the understanding of prolapse related outcomes, individual items of the POP − SS will also be analysed separately and an additional dichotomous POP − Q measure (above/below the hymen) will be included in the analysis.

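### The stated 80% power does not follow from the Sample size section's own paired inputs: 120 pairs give 97.7%, and 62 pairs give 80%

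*Protocol article*

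**What the plan says.** The Sample size section supplies every input to the calculation:

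- Target difference: "We have assumed that the minimum clinically important difference in the POP − SS is 2".
- Variability: "the standard deviation of the differences in POP − SS between baseline and one year will be 5.5 (as observed in POPPY").
- Error rate: "with 2-sided alpha = 0.05".
- Size and design: "A sample size of 120 paired observations".
- Result: these inputs "will therefore provide 80% power to detect important differences in" POP-SS from baseline to one year.

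The analysis section (Data analysis, B) Outcomes data) names a test that fits this design: "We will initially examine the differences before and after intervention using paired t-tests and chi-square tests". The same section says "Complete case analyses will be performed throughout", with multiple imputation kept for secondary analyses. Under Recruitment/sampling the target is again 120: "We aim to recruit 120 women to the outcomes study".

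**The concern.** The section presents 80% as the direct consequence of the inputs it lists, so the figure can be checked without any outside source. A paired comparison with a standardised change of 2/5.5 = 0.364 should need far fewer than 120 pairs for 80% power. Either the power is misstated or one of the inputs is not what its label says.

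This is the only power statement in the article, and it concerns the primary outcome. A reader takes from it that 120 complete pairs are only just enough for a 2-point change. On the stated inputs about half that number would do. A shortfall in recruitment or follow-up would be judged against the wrong benchmark, and anyone reusing the calculation would roughly double their sample. If the SD is the part that is wrong, the true margin is much smaller than the stated inputs imply.

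A smaller point goes with it. The same 120 is used for women recruited and for baseline-to-one-year pairs. Under complete-case analysis the two agree only if no woman is lost.

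**Working it through.** **Inputs** (all from Sample size): difference δ = 2; SD of within-woman differences σ = 5.5; two-sided α = 0.05; n = 120 pairs. The test is the paired t-test named under Data analysis, B) Outcomes data.

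**1. Trying to reproduce the 80%.** The paired t-test has n − 1 = 119 degrees of freedom and non-centrality δ/σ × √n = (2/5.5) × √120 = 0.364 × 10.954 = 3.98. Power from the non-central t is **97.7%**. The normal approximation gives Φ(3.98 − 1.96) = Φ(2.02) = 97.8%. The 80% is not reproduced, and the gap is far larger than rounding or the choice between t and normal.

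**2. Pairs needed.** Normal approximation: n = [σ(z₀.₉₇₅ + z₀.₈₀)/δ]² = [5.5 × (1.960 + 0.842)/2]² = 59.4, so 60. By the t distribution, 61 pairs give 79.8% and 62 give 80.5%, so **62 pairs** for 80%. For 90% power it is 82 pairs.

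**3. What 120 pairs would detect.** Holding σ = 5.5 and power at 80%, the detectable change is **1.42 points**. Holding δ = 2, the SD of differences would have to be 7.76 for 120 pairs to give 80%.

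**4. Could an unstated allowance close the gap?** Keeping the paired design and the stated SD, 120 falls to 80% power only with one of these:

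- loss of about 48% (1 − 62/120);
- a design effect of about 1.94 (120/62);
- a two-sided α of about 0.0022.

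The section mentions none of them.

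**5. Calculations that do land near 120.**

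| Reading | Result |
|---|---|
| Independent two-sample t-test, δ = 2, SD 5.5 | 119.7, so 120 per group; power at 120 per group 80.1% |
| The same by normal approximation | 2 × 59.36 = 118.7, so 119 per group |
| Paired test, 5.5 taken as the SD at a single time, correlation 0: SD of differences = √2 × 5.5 = 7.78 | Power at 120 pairs 79.8% |

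These are nearly the same arithmetic, because each doubles the variance. The match cannot tell a wrong formula from a wrongly labelled SD.

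**6. Loss to follow-up.** The article gives no loss rate, so a range is assumed. All rows take σ = 5.5 and independent women.

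| Assumed loss at one year | Complete pairs | Power for 2 points |
|---|---|---|
| 0% | 120 | 97.7% |
| 10% | 108 | 96.3% |
| 20% | 96 | 94.1% |
| 30% | 84 | 90.9% |
| 40% | 72 | 86.1% |

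**The case against.** The best defence is that the error is harmless. It runs in the safe direction: 120 women exceed what the stated aim needs, power stays above 90% with an assumed 30% loss, and no test, estimate or recruitment target changes. This stands, and it limits how serious the point is. It does not make the 80% correct.

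A second defence is that 120 includes a margin for attrition or for clustering by therapist or site. Clustering is plausible: there are five sites, and each staff member is expected to recruit about five women. If changes in POP-SS were correlated within clusters, 97.7% would be too high. As an illustration, a design effect of 1.94 corresponds to an intraclass correlation of about 0.94/23 = 0.04 with 24 women per site (120/5), or about 0.94/4 = 0.23 with five women per therapist. These correlations are back-calculated, not taken from the article. So 97.7% must be quoted as assuming independence. But the Sample size section makes no such adjustment and derives 80% from the unadjusted inputs, so the defence would supply a reason that the text does not give.

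Third, a condensed article may leave a dropout allowance to the full protocol. That is fair. The absence of an allowance is not the finding, and the double use of 120 adds little weight, since plausible loss does not threaten power. A full protocol or SAP cannot, however, make a wrong figure in the article right.

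Two stronger readings are tempting. A reader might infer that the two-sample formula was used by mistake, because 120 matches it exactly. The article does not say how 120 was obtained, and the mislabelled-SD route fits almost as well. A reader might also infer that the study is badly sized, either recruiting twice too many women or falling short once some are lost. Neither is supported: the article has further aims beyond the overall before-after test, and that test keeps ample power on the stated inputs.

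**Conclusion.** The point holds as an error of statement. With the section's own inputs, 120 pairs give 97.7% power, not 80%; 62 pairs suffice for 80%; and 120 pairs detect about 1.42 points, not 2, with 80% power. Nothing elsewhere in the article corrects this.

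The figures rest on two assumptions: that 5.5 is the SD of within-woman changes, as labelled, and that the women are independent. If the first fails, 97.7% and 62 fall with it. An SD of differences near 7.8 would put 120 pairs at about 80%, with nothing in hand for loss. That cannot be settled from the article, because the POPPY data behind the 5.5 are not shown.

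On the stated inputs the error is conservative for the before-after comparison and does not threaten its conclusion. The paragraph needs correcting; the recruitment target does not.

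**What to change.** 1. Check against the POPPY data whether 5.5 is the SD of within-woman changes from baseline to one year.
2. If it is, restate the result, for example: *With an SD of differences of 5.5 and two-sided alpha 0.05, 62 pairs give 80% power to detect a 2-point change; 120 pairs give about 98%, before any allowance for clustering by therapist or site.*
3. If it is not, give the correct SD of differences and recompute the power from it.
4. Give 120 as the number recruited, and state power for the complete pairs expected at one year with the assumed loss shown. With 20% to 30% loss and an SD of 5.5, that is 96 to 84 pairs and 94% to 91% power.
5. Do not describe the surplus over 62 as an allowance for attrition or clustering unless that was the actual reason for choosing 120.

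The cost is one check of a source figure and one rewritten paragraph. Recruitment stays as planned.

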### Setting

The outcomes study will be based at five sites, those three taking part in the RE plus two further sites who will be recruited to specifically take part in the outcomes study (see Table 1). Clinicians identified locally at each site will be trained to deliver the PFMT intervention by Pelvic, Obstetric and Gynaecological Physiotherapy approved trainers.

### C) Economic evaluation

An economic evaluation will compare costs and outcomes of the different models of service delivery.

## The PFMT intervention

PFMT refers to the regular practice of repetitive pelvic floor muscle contractions in order to produce a training effect on the muscles. The aim of a PFMT programme is to increase the strength of the muscles to build up muscle volume thereby improving structural support, increase endurance, improve resting tone, improve muscle fibre recruitment through improved nerve function and properties of muscle fibres; and improve cognitive awareness of body posture and a relaxed versus an un-relaxed state of the pelvic floor [17]. To produce improvements in muscle strength and endurance the basic physiological principles must be adhered to [18]. These include: overload (muscles need to perform more work than usual resulting in fatigue); specificity (muscles must be trained with physical activity that replicates as closely as possible the functional movement required); maintenance and reversibility (benefits of the exercise are reversible if they are not undertaken on a regular basis). Evidence suggests that for effective strength training in skeletal muscles in adults, three to five sets of 8 to 12 slow velocity, close to maximal contractions per day should be performed 2 to 5 days per week for 16 weeks [19].

The PFMT protocol will normally be delivered during five therapy appointments at weeks 0, 2, 6, 11, 16 with fewer or more appointments as judged by therapists based on client needs. The intervention will normally last 16 weeks. Each of the five appointments will take around 30 min each, with the initial appointment expected to take longer (45–60 min). The initial assessment appointment will elicit and record basic demographic and medical history along with a visual and digital assessment of the vagina and pelvic floor muscles. The initial assessment aims to provide accurate knowledge of the condition of the perineum and vagina, the woman’s capacity for contracting and relaxing her pelvic floor muscles and the influence of muscles on any visible or palpable prolapse. This information is recorded using the Oxford Classification (PERFECT scheme) and provides a basis for determining the dose/frequency of PFMT [20].

Women are taught the correct exercise technique and this is confirmed on digital palpation by the therapist with the woman in the supine position. Women are encouraged to become aware of contracting and holding the muscles, and also of relaxing them. This is facilitated by the use of different exercise positions (e.g. side lying), counter pressure on their perineum, coordination of contraction/relaxation with breathing. Women are taught to counterbrace, that is, to pre-contract their pelvic floor muscles prior to an increase in intra-abdominal pressure (e.g. coughing, sneezing, lifting), a technique known as “the knack” [21].

The initial exercise programme is identified and agreed between the woman and therapist over the first and second appointments, according to the woman’s ability. The exercise programme is practised during subsequent appointments to allow the therapist to assess progress and adjust the programme as necessary. Home exercise may be prescribed from the first appointment, or as soon as the therapist confirms a correct technique has been achieved.

Home exercise is tailored to the individual woman, ensuring a training effect on the muscles is achieved, but that the programme is manageable for the woman. Targets of maximum strength, endurance and repetitions are set, aiming towards a programme of three to five sets per day of 10 maximum strength pelvic floor muscle contractions, holding each contraction for up to 10 s with a 4 s rest between contractions, followed by up to 50 fast contractions. Exercise position is varied (lying, sitting, standing, squatting). Potential for progression is determined during the therapy appointments and is carried over to home exercise. Progression is tailored for each woman [18] and consists of increased number of contractions, increased length of hold, decreased rest periods and the introduction of more difficult positions. Therapists will make use of appropriate motivational techniques and advice detailed within the protocol to encourage correct exercise technique and adherence to the prescribed programme. Women with urinary and/or bowel symptoms including urgency, frequency, incontinence and defecation difficulties will be given advice on to improve these symptoms.

Vaginal examinations will be undertaken following Chartered Society of Physiotherapy and Royal College of Obstetrics and Gynaecology guidelines for performing intimate examinations. Local infection policy will be adhered to and the woman’s informed consent will be obtained. A chaperone will be offered. Repeat pelvic floor muscle assessments will be undertaken at each session to assess progress and modify home exercises if the woman is agreeable.

